## Abstract

**Aims:**

To assess the impact of the COVID-19 pandemic on the health condition of people ≥75 years of age and on their family caregivers in Spain.

**Design:**

Multicentric, mixed method concurrent study.

**Methods:**

This work, which will be conducted within the primary care setting in 11 administrative regions of Spain, will include three coordinated studies with different methodologies. The first is a population-based cohort study that will use real-life data to analyze the rates and evolution of health needs, care provision, and services utilization before, during, and after the pandemic. The second is a prospective cohort study with 18 months of follow-up that will evaluate the impact of COVID-19 disease on mortality, frailty, functional and cognitive capacity, and quality of life of the participants. Finally, the third will be a qualitative study with a critical social approach to understand and interpret the social, political, and economic dimensions associated with the use of health services during the pandemic. We have followed the SPIRIT Checklist to address trial protocol and related documents. This research is being funded by the Instituto de Salud Carlos III since 2021 and was approved by its ethics committee (June 2022).

**Discussion:**

The study findings will reveal the long-term impact of the COVID-19 pandemic on the older adults and their caregivers. This information will serve policymakers to adapt health policies to the needs of this population in situations of maximum stress, such as that produced by the COVID-19 pandemic.

**Trial Registration:**

Identifier: NCT05249868 [ClinicalTrials.gov].

## 1 Introduction

The coronavirus disease 2019 (COVID-19) has caused a significant social and economic impact worldwide since the appearance of the first cases in the city of Wuhan (China) (1). The pandemic forced public health authorities to impose drastic measures as an epidemiological containment strategy. The Spanish government decreed a state of alarm across the national territory on March 14, 2020, which limited the free movement of citizens to essential acts and ordered home confinement for the population. In other countries, in addition to these measures, public transportation was shut down (2). Ninety-eight days later, on June 21, the state of alarm came to an end.

On a worldwide level, containment measures to reduce disease transmission were effective, especially home confinement (3), although they also entailed a substantial social impact (4) and a negative effect on physical activity levels, sleep quality, and wellbeing (5). These unprecedented measures, along with the rapid and unpredictable evolution of the pandemic, caused natural responses of fear, stress, anxiety, and loneliness among the population (6). Furthermore, the self-care and health management in people suffering from multiple comorbidities and preexisting mental disorders were adversely affected by the subsequent difficulties in accessing social-health services (7).

Numerous studies have analyzed the impact of the COVID-19 pandemic and the adopted preventive measures on the population. The social-distancing regulations imposed in all countries to control the pandemic have brought significant psychosocial consequences for individuals (8, 9).

This impact has been especially noteworthy in vulnerable groups such as children, migrants, people at risk of exclusion, individuals with psychiatric pathology, the older adults, and caregivers (8). The lock-down has been specially difficult to the older adults people, in terms of shielding and self-isolation. The lack of social communication and community networking could have affected the older adults's mental health, as well as the engagement with their own health needs and management (10).

Additionally, the technological gap experienced by these groups has aggravated this effect, increasing their anxiety levels and sense of abandonment (11). A qualitative study (12) reported repercussions on the emotional experience, coping resources, and the information received, as well as difficulties in self-care and access to health services for this vulnerable population, all while suggesting lessons to be learned for the future.

Social support is one aspect that may have influenced these results, as it is a natural tool for coping with traumatic situations and a good predictor of the resilience that a person will exhibit after a stressful experience (13). Nevertheless, support networks have not been sufficiently studied, despite their relevance for the older adults or dependents throughout the pandemic (14). Loneliness and isolation are associated with reduced longevity and worse health perception (15). Increases in sedentary activities and reductions in physical activity (16) can exacerbate frailty, and dependency for basic activities of daily living (17).

During the first weeks of the pandemic, the Spanish health system was overwhelmed by the high number of cases, which led to a reorganization and reorientation of health services in the following months according to the European Union recomendations. The growing needs of the vulnerable population during the pandemic, together with the fact that professional care was reduced, implied an overload of care for family caregivers. These were often forced to reorganize the family and care structure (17), with the added difficulty that it was not always possible for them to access the dependent's home for care (9).

In light of the above, characterizing the change in care needs of this population and the impact on their utilization of services is warranted. Standardized nursing languages (SNLs) are powerful descriptors of conditions requiring care (18). SNLs also allow for identifying situations of dependence and vulnerability, as well as describing care needs on a large scale (19). Specifically, nursing diagnoses recorded in electronic medical records (EMRs) show good predictive value to use social and healthcare resources (18).

Analyzing the utilization of health services through the evolution of SNLs in EMRs in conjunction with a mixed-methods approach (20) will provide insights into the medium- to long-term health impact, how the reorientation of services has occurred, and the experiences of the older adults and their family caregivers.

## 2 Methods

### 2.1 Aims

The main aim is to assess the impact of the COVID-19 pandemic on the health condition of people aged ≥75 years in Spain. Specifically, this study aims at:

Analyzing the evolution of the rates of needs, provision of care, and utilization of services using data from primary care EMRs during 2018–2023, as well as describing its geographic distribution.Assessing the impact of COVID-19 on mortality, frailty, functional and cognitive capacity, and quality of life of healthcare users.Understanding and interpreting the social, political, and economic dimensions associated with the use of health services by individuals aged ≥75 years and their family caregivers during the pandemic.

### 2.2 Design/methodology

#### 2.2.1 Study design and setting

Multicentric, mixed models study combining quantitative and qualitative methodologies. The study will be conducted in the primary care setting of 11 of the 19 Spanish administrative regions and will include both insular and peninsular, rural and urban populations, as well as different socioeconomic levels. Three separate studies will be conducted to provide answers to each specific objective, as described below. Integration will be addressed in the methodological level through connecting, to help to understand contextual factors in the quantitative phase or in the selection of participants in the qualitative phase, Integration will also be tackled at the Interpretation and Reporting Level, integrating the findings through narrative in a stage approach, where the results are analyzed and published separately (21).

We have followed the SPIRIT Checklist to address trial protocol and related documents.

The general study design can be found in Figure 1.

**Figure 1 F1:**
[figure not shown]
General study design.

#### 2.2.2 Prospective study of an ambispective cohort, with a multipurpose approach, real-life data, and a follow-up of 6 years

##### 2.2.2.1 Population

People aged ≥75 years in January 2018, assigned to any of the health centers of the Spanish National Health System in one of the 11 regions participating in the study. They must have at least one entry in the EMR during 2018, not be institutionalized, and not be mutualists at the time of the cutoff. No sampling is performed, because data will be extracted from the whole population that meets the inclusion criteria.

##### 2.2.2.2 Data source

Primary care EMRs.

##### 2.2.2.3 Variables

Sociodemographic and clinical data; functional, cognitive, and mental status; frailty; social risk; functional patterns; nursing diagnoses, outcomes, and interventions; and use of health services.

##### 2.2.2.4 Data collection

A protocol for standardized variables will be developed based on the Minimum Basic Data Set for Primary Care (MBDS-AP), defined by the Spanish Ministry of Health. Information recorded under real clinical practice conditions between 2018 and 2023 will be extracted from the EMRs. To standardize the variables collected, we used as a reference the consensus document of the Ministry of Health called the Primary Care Clinical Database (BDCAP), which standardizes the measurement instruments and the typology of the variables collected in the electronic medical record throughout the country.

##### 2.2.2.5 Analysis

The study will describe the included population, their care needs, and nursing interventions, all with 95% confidence intervals (CI). The use of health services will be reported as the utilization rate per 1,000 person-year. Incidence rates of new diagnoses and interventions will be calculated per 1,000 person-year with their 95%CI for each follow-up year. The evolution of diagnoses and interventions will be examined using time series analysis. Finally, the geographical distribution of needs will also be described.

#### 2.2.3 Cohort study with a follow-up of 18 months

##### 2.2.3.1 Population

Based on the population of the prospective study, the participants will be ≥75 years of age, with at least one record in the last half of 2019 and another one in the first half of 2022, will not be institutionalized, and must provide informed written consent. Subjects with sensory deficits, cognitive impairment, a Barthel ADL index ≤ 5 points, life expectancy ≤ 9 months, or participants transferred during the recruitment period will be excluded.

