##### 2.2.3.3 Recruitment

A total of 105 clinical nurses from the participating centers will be recruited and trained. From the previously selected sample, each nurse will invite 10 candidates from their health center to participate (seven unexposed and three exposed), after ensuring that they meet the inclusion and exclusion criteria.

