##### 2.2.3.4 Variables

The exposure variable will be SARS-CoV-2 infection confirmed by diagnostic testing between May 11th of 2020 and the recruitment start date. The outcome variables will be mortality, functionality (Barthel scale), quality of life (EuroQol-5D), mental health (Hamilton depression rating scale), cognitive capacity (Mini-Mental State Examination), and frailty (Frailty index). In addition, sociodemographic (age and gender) and clinical, infection-related, and pandemic-context variables will be recorded. The date of the infection diagnosis and length of hospitalization will also be recorded for the cohort of exposed patients, as well as diagnoses of infection during the follow-up for the cohort of unexposed patients.

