The analysis of real-life data, obtained from a cohort from 11 Spanish regions representative of the peninsular and insular population, rural and urban setting, will favor the external validity of the results and allow their extrapolation to similar contexts. These data will be of great epidemiological value, as the estimated study population exceeds 1.5 million primary care users and the information will be collected in routine clinical practice, including nursing diagnoses. In addition, the collected data will allow observing the changes in the demand for health resources, occurred during and after the pandemic, based on the information automatically generated by the system (e.g., number and types of consultations). By following up two cohorts over 18 months, this study aims to explore if there have been changes in the aging process of the included population and whether these may be due to the biological impact of the disease, or the situation experienced during the pandemic.

One strength of this study to highlight is the robustness of the outcome variables, which are mostly self-reported outcomes or from EMRs and SNLs registries. The enrolment and follow-up of participants will be conducted by their assigned primary care nurses, which will minimize dropouts and increase the quality of records. In order to avoid selection bias, the cohort of subjects exposed to COVID-19 will only include those individuals diagnosed after May 11th of 2020, as that was the time point at which the diagnosis required confirmatory testing in Spain.

The qualitative methodology uses interviews and focus groups to provide a vision of the reality experienced by the study population. This approach will allow understanding and interpreting the social, political, and economic dimensions associated with the use of health services by patients and caregivers.

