### 3.1 Limitations

The quality and homogeneity of data obtained from EMRs can entail a limitation. To overcome this, some of the database sources have been previously validated in epidemiological studies, standardized variables have been selected, and the research team will endeavor to standardize the selected data. A survival bias that underestimates the effect of the disease is another potential limitation inherent to cohort follow-up. For the qualitative fieldwork, the complexity of the studied population may pose difficulties in terms of discourse saturation and narrative quality. This complexity has been taken into consideration by proposing sufficient time slots for the sample selection and data collection processes. For the organization of focus groups, various available schedules will be offered to meet the time needs of the caregivers.

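### 18-month cohort: an infection recorded in January–June 2022 can itself meet the record requirement, so eligibility depends in part on exposure status

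*Protocol article*

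**What the plan says.** Section 2.2.3.1 draws the 18-month cohort from the population of the first study and requires people "with at least one record in the last half of 2019 and another one in the first half of 2022". The rule is the same for both cohorts and does not restrict the type of record or the reason for it. The source population (section 2.2.2.1) already carries a contact condition: "They must have at least one entry in the EMR during 2018".

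Section 2.2.3.4 defines exposure as "SARS-CoV-2 infection confirmed by diagnostic testing between May 11th of 2020 and the recruitment start date". No calendar date is given for the recruitment start. The abstract dates ethics approval to June 2022.

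Section 2.2.3.3 sets the split by quota: "each nurse will invite 10 candidates from their health center to participate (seven unexposed and three exposed".

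Two passages deal with selection. Section 3 addresses the opening of the exposure window: "In order to avoid selection bias, the cohort of subjects exposed to COVID-19 will only include those individuals diagnosed after May 11th of 2020". Section 3.1 adds: "A survival bias that underestimates the effect of the disease is another potential limitation inherent to cohort follow-up". Neither mentions the record requirement.

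**The concern.** A rule about records looks neutral because it is worded identically for both cohorts. It is not neutral when the exposure itself creates a record inside the qualifying window. Take two people with the same health and the same habit of rarely attending. The one with a confirmed infection in, say, February 2022 has an entry and is eligible. The one who was never infected, or whose infection was in 2020 or 2021, has no entry in that half-year and is not. Some of the exposed cohort may therefore be people with few contacts who have no counterpart among the unexposed.

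At stake is the comparability of the two cohorts on function, frailty and quality of life. If people with few contacts decline less than others, their presence among the exposed alone would dilute the estimated effect of infection.

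**Working it through.** **Step 1. The planned contrast.** Section 2.2.3.2 gives 47% with a change in functionality below 5 points among the unexposed, a 10% decrease among the exposed, a 2:1 ratio, 80% power and 20% dropout. Reading the decrease as 10 percentage points (47% to 37%):

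- Hazard ratio = ln 0.37 / ln 0.47 = 1.317.
- Events = (1.96 + 0.8416)² / [(1/3)(2/3)(ln 1.317)²] = 467 (unrounded inputs, rounded up).
- Mean event probability = (2/3)(0.53) + (1/3)(0.63) = 0.563, so N = 467 / 0.563 = 829, and 829 / 0.80 = 1,037.

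The article states 1,035 (690 + 345), so the figure reproduces closely. A relative decrease of 10% (to 42.3%) would need about 4,700 to 4,900. The contrast is therefore 53% against 63% with a change of 5 points or more. The concern is about who enters and does not alter N.

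**Step 2. Do the windows overlap?** From 11 May 2020 to 1 January 2022 is 600 days, and January–June 2022 has 181. For assumed recruitment starts:

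- 1 April 2022: 90 of 690 days overlap (13%).
- 1 June 2022: 151 of 751 (20%).
- 1 July 2022: 181 of 781 (23%).
- 1 October 2022: 181 of 873 (21%).

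Only a start by 1 January 2022 gives no overlap. That is hard to reconcile with a criterion that uses 2022 records and with approval in June 2022. These are shares of calendar time, not of infections.

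**Step 3. Eligibility by exposure.** Let c be the probability of a January–June 2022 record other than the infection entry, and f the share of exposed people infected in that half-year. Assume every such infection leaves a record, and that c is the same in all groups.

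- Unexposed, and exposed people infected at other times: c.
- Exposed overall: c + (1 − c)f.
- Share s of the eligible exposed who qualify only through the infection: (1 − c)f / [c + (1 − c)f].

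The documents give neither c nor f, so the values below are assumptions. The last column is the shift in the exposed risk if these people had half the risk of the other exposed (also an assumption): 63 × 0.5 × s.

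| c | f | Eligibility ratio, exposed : unexposed | s | Of 345 | Shift, points |
|---|---|---|---|---|---|
| 0.98 | 0.20 | 1.004 | 0.4% | 1 | −0.1 |
| 0.95 | 0.50 | 1.03 | 2.6% | 9 | −0.8 |
| 0.90 | 0.235 | 1.03 | 2.5% | 9 | −0.8 |
| 0.90 | 0.70 | 1.08 | 7.2% | 25 | −2.3 |
| 0.80 | 0.50 | 1.13 | 11.1% | 38 | −3.5 |
| 0.70 | 0.70 | 1.30 | 23.1% | 80 | −7.3 |

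The ratio exceeds 1 whenever c < 1 and f > 0. Because quotas fix the group sizes, the consequence is composition, not numbers.

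**Step 4. Direction and limit.** For a general risk ratio r in these people, the shift is 63 × (r − 1) × s. It is negative if r < 1, zero if r = 1 and positive if r > 1, and the documents do not give r. With r = 0.5, cancelling the 10-point contrast would need s = 10 / (63 × 0.5) = 31.7%, above every row.

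**The case against.** The case on the other side has several parts, and much of it stands.

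- **Record is undefined.** If a positive test counts, then for the unexposed so does a negative test, a preventive visit or an administrative entry. A reader might infer that the unexposed cohort is enriched for people needing care. The documents do not support that. What remains is that the unexposed need some entry that infection did not supply.
- **Everyone is already selected for contact.** Participants were 75 or older in January 2018, with an entry in 2018 and another in late 2019. They must also be invited by a nurse from their own centre and give consent. This makes c probably high and the effect probably small.
- **Only part of the exposed cohort is affected.** Those infected before January 2022 meet the same requirement as the unexposed.
- **Direction is open.** Few contacts may mean good health. But the introduction describes vulnerable older people with difficulty reaching services, and for them few contacts may mean isolation or frailty, which would push the bias the other way.
- **Baseline status is measured directly.** Barthel, EuroQol-5D, Mini-Mental State Examination and frailty index are collected on everyone at enrolment, and the Cox models adjust for clinical characteristics. It would be wrong to say that adjustment rests on recorded diagnoses alone. It is still only a partial remedy, because baseline follows the infection and may already carry part of its effect.

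A reader might also infer that the infection effect could be reversed. Under the halved-risk illustration even the most extreme row leaves 10 − 7.3 = 2.7 points in the expected direction.

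None of this removes the overlap itself. Section 3 treats only the start of the exposure window, and section 3.1 only survival. Both rules are stated in the article, so the problem comes from what it fixes, not from what it leaves to a fuller document.

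**Conclusion.** The point holds as a limited design flaw. As worded, an infection recorded in January–June 2022 can confer eligibility, so exposure status helps decide who enters. This rests on two readings: that recruitment began after 1 January 2022, which is inferred, and that an infection entry counts as a record, which is the plain wording.

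The size is not derivable from the documents. The assumed ranges span about 1 to 80 of 345 exposed participants, and the earlier record requirements point to the low end. Attenuation is plausible if people with few contacts are healthier, but the direction is not established. It is worth correcting because the correction is cheap, not because a large bias has been shown.

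**What to change.** Before lists go to the nurses, make either of these changes:

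- Count toward the first-half-2022 requirement only records unrelated to SARS-CoV-2 testing, diagnosis or follow-up, applied identically to both cohorts. Eligibility is then c in both and the ratio returns to 1.00 under the assumptions above.
- Replace the 2022 record requirement with being alive and assigned to the centre on one fixed date for everyone.

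Either is a change to the sampling query. The cost is a slightly smaller eligible pool under the first option.

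Section 2.2.3.5 speaks of data collection partly in the past tense, so sampling may be complete. In that case, run a sensitivity analysis restricted to participants with a record unrelated to SARS-CoV-2 in January–June 2022, which needs a look-up in the medical record. Alternatively, exclude exposed people infected in that half-year; the infection date is already collected under section 2.2.3.4, so this needs no new data. The second version also lengthens the average time since infection, so a different result would not by itself prove selection bias. Both reduce the analysis set. Add the limitation to section 3.1 alongside survival bias.

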##### 2.2.3.2 Sample size

Based on the assumption of a proportional hazards model for survival times, the sample size was estimated to allow the comparison of two curves. The probability of a change in functionality of < 5 points at 18 months was previously estimated to be 47% in the unexposed group (22) and this figure was considered to decrease by at least 10% in exposed patients. Considering a ratio of 2:1 between the sample sizes of the unexposed and exposed groups, for a CI of 95%, a power of 80%, and a dropout rate of 20%, the sample size was calculated to be 1,035 subjects (690 unexposed and 345 exposed). A randomized sampling by quotas for the included health centers in each of the regions will be performed.

